**Figure 3 fig3:**
[figure not shown]
Algorithm steps for skin masking **(A)**, lesion detection **(B)** and lesion segmentation **(C)**. A three-step approach is used for lesion detection and segmentation. **(A)** as image tiles may include background of non-skin area, a skin mask obtained by thresholding of HSV color space, is applied to minimize inaccurate detections on non-skin area. **(B)** YOLO (You Only Look Once) (27) model, pretrained on COCO (Common Objects in Contexts) (28) dataset, is adapted to our datasets to detect skin lesions, depicted as bounding boxes. **(C)** The bounding box predictions are used as prompts for segmentation, leveraging SAM (Segment Anything Model) (29) model to provide precise segmentation of skin lesions.

#### Inter-exploration lesion matching

The objective of this task is to pinpoint the most optimal view, specifically the one that appears most orthogonal to the camera, for each detected lesion on the patient. With the help of the patient’s body geometry (i.e., acquired and properly anonymized 3D model), along with the system’s geometric calibration parameters, informed predictions can be made regarding the location of each lesion within the image tiles and approximate their image coordinates in each tile (with a margin for calibration error). To refine the predicted location based on the system geometry, we take advantage of the image information and perform feature matching in a subsequent step, either based on lesion or image features, to obtain a more precise lesion location.

Once all the views corresponding to a particular lesion are identified, the best view is selected based on its positioning within the patient’s 3D model in relation to the camera system’s geometry. This optimal view for each lesion is then extracted from its respective image tile, resulting in a collection of cropped individual lesion images. This process is illustrated in Figures 4A–D.

**Figure 4 fig4:**
[figure not shown]
Steps involved in inter-exploration lesion matching and change detection. **(A)** First image exploration (i.e., image capture). **(B)** Second image exploration (e.g., 6–12 months later). **(C)** Feature matching between sequential explorations. **(D)** Transformed first image exploration to match second image exploration. **(E)** Segmentation mask for first image exploration. **(F)** Segmentation mask for second image exploration. **(G)** Detected differences between explorations.

#### Super-resolution

Machine learning models, particularly deep learning models, trained on high-resolution data tend to perform worse when applied to real-world scenarios, where image quality may vary. Methods to enhance fine details and subtle features in lower-resolution images allow for more precise analysis. Super-resolution techniques can significantly improve the visual quality and sharpness of images. By applying this technique to the collection of cropped individual lesion images, high-resolution versions of the images can be generated, which are visually more appealing and detailed, and can improve the performance of the trained models.

For image super-resolution, the GAN prior embedded network (GPEN) (30) is used on the lesion crops. We fine-tune the GPEN model, which initially utilizes pretrained weights from the FFHQ (Flickr-Faces-High-Quality) dataset (31) on our own generated data, including artificially degraded dermoscopy images from the International Skin Imaging Collaboration (ISIC) challenge dataset (32). This degradation process includes resizing, blurring, and adding noise to the original images. It enables the model to be fine-tuned to match our specific super-resolution needs and achieve image quality as close as possible to dermoscopy.

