#### Image acquisition

All participants underwent 3D total body photography using the VECTRA WB360 whole body 3D imaging system (Canfield Scientific Inc., Parsippany, New Jersey, United States). In Barcelona, TBP was conducted prospectively (after consent signed); in Brisbane retrospective TBP image archives were accessed after consent to participate was provided. The VECTRA WB360 system is a framework of 92 cameras, in which a study participant is asked to stand, holding a specific anatomical pose. All 92 cameras simultaneously capture images of the patient, and software is used to construct a 3D avatar from those images. An attached dermoscopy camera (Visiomed D200e dermatoscope, Canfield Scientific), allows additional high-resolution images of single lesions to be recorded and mapped to the 3D avatar. This 3D Imaging System enables the objective documentation of all skin lesions (excluding scalp, soles of feet and any skin covered by underwear) and facilitates the monitoring of changes over time.

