### Image annotation for diagnostic categories

A second round of annotation is completed by expert dermatologists, or dermatologically trained clinicians, for the diagnostic categories displayed in Table 1. This process is to be completed by the two recruitment sites (Barcelona and Brisbane), as well as an additional clinical site, the University of Trieste, Trieste, Italy.

**Table 1 tab1:** Final diagnostic categories for lesion annotation, with shorthand acronym in brackets.

Diagnostic categories for annotation	Shorthand
Benign melanocytic lesion	BM
Suspicious melanocytic lesion	SM
Melanoma	MM
Solar Lentigo	SL
Seborrheic Keratosis	SK
Angioma	AG
Actinic Keratosis/Intraepidermal carcinoma	AK/IEC
Dermatofibroma	DF
Basal Cell Carcinoma	BCC
Squamous Cell Carcinoma	SCC
Inflammatory Lesion	IL
Collision Tumor	CT
Unknown	UN
Other	OT

This is conducted using V7’s Darwin platform and verified through VECTRA WB360 DermaGraphix Software. The image tiles annotated in the Darwin platform are reconstructed and projected back to the 3D TBP image for native visualization in the DermaGraphix software. This software allows the expert dermatologist to view the annotated lesions with the 3D avatar as a reference, with the ability to further annotate each lesion into diagnostic categories. The diagnostic classes for annotation were selected to be appropriate for the lower resolution of TBP images (as compared to dermoscopy). The diagnostic hierarchy available for melanocytic lesions (benign, suspicious, melanoma), reflect increasing levels of confidence in lesion categorization, including the pre-annotation of color.

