## Discussion

To our knowledge, this protocol is the first to describe the multiclass annotation of total body photography (TBP) for both skin lesion and phenotype characteristics. This includes DICOM labelled patient-level metadata designed for machine learning application. Algorithms developed with these datasets will address several clinically relevant gaps that previous skin lesion classifier algorithms often lack (49). The majority of algorithms to date are trained to consider a dermoscopic image of a lesion, in isolation of any clinical background. This has negatively impacted the translation of this technology into clinical practice. In a real-world scenario, a dermatologist would consider a patient’s medical history, phenotype (including skin/hair/eye color, nevi characteristics, and UV damage), review sequential imaging to detect lesion changes, and apply ‘ugly duckling’ methods, which draws attention to lesions that are unlike others on a given patient. The aim of this protocol is to develop computer aided diagnostic (CAD) tools capable of providing holistic risk assessment of both patient and individual lesions.

One advantage this protocol presents is the prospective collection of TBP from patients at various risk of melanoma, providing a representative image dataset of the entire skin surface for both general and higher risk populations. To date, algorithms for skin lesion classification are often developed using retrospective public datasets of mostly dermoscopy images, which may be restricted to ‘interesting cases’ and lack generalizability to day-to-day clinical practice (6). Furthermore, an algorithm applied to TBP or other wide-field clinical images, increases usability as a triage tool by non-dermatologists. Any AI triage tools dependent on dermoscopy images, must assume that the end-user has professional training to identify lesions requiring specialist review. In the scenario of a telehealth TBP appointment where dermatologists are not involved in the imaging, the imaging technicians could be prompted by AI tools to take additional dermoscopy images of lesions flagged as suspicious or malignant.

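### Lesion crops pass through a generative super-resolution network tuned partly on degraded dermoscopy, and the benefit to the classifier is assumed, not tested

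*Protocol article*

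**What the plan says.** All references are to the protocol article.

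- Super-resolution names the network and its target images: "the GAN prior embedded network (GPEN) (30) is used on the lesion crops". It starts from weights learned on a face dataset and is fine-tuned "on our own generated data, including artificially degraded dermoscopy images from the International Skin Imaging Collaboration (ISIC) challenge dataset". The degradation consists of resizing, blurring and adding noise. The aim is given as "It enables the model to be fine-tuned to match our specific super-resolution needs and achieve image quality as close as possible to dermoscopy". The section says that the sharper images can improve model performance, and it describes no check of this.
- Skin lesion classification builds the classifier on cropped single-lesion images produced by the preceding steps. Super-resolution is the step immediately before it. The images are put at about 210 × 210 pixels, without saying whether this is before or after super-resolution. The one experiment mentioned is the choice among EfficientNet B0 to B3.
- Image acquisition describes 92 cameras that capture the standing participant. A separate attached dermatoscope "allows additional high-resolution images of single lesions to be recorded and mapped to the 3D avatar".
- The sections on ugly-duckling detection, lesion risk assessment and explainable AI use, in turn, the classifier's last-layer features, its diagnosis, and the relevance of its input pixels.

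**The concern.** A network trained to restore dermoscopy images that were shrunk, blurred and noised learns to put dermoscopic structure back. A body-photograph crop has not lost such structure through blurring. It was taken by a different device at a distance, and may never have recorded it. Detail beyond what the photograph holds must come from the network's prior.

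If the classifier reads those crops, its diagnosis may rest in part on generated structure. Features could be drawn onto an ordinary lesion, or real irregularity could be smoothed away. The explanation maps could then direct a clinician to structure that was not photographed. One preprocessing step would reach most lesion-level outputs, on the strength of a benefit that the article only asserts.

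**Working it through.** **Step 1. Is the step fixed, and what does it reach?**

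| Section | What it contributes |
|---|---|
| Super-resolution | Network applied to the lesion crops; dermoscopy-like quality is the target |
| Skin lesion classification | Input is the crops from the earlier steps (implied, not stated, to be the super-resolved ones) |
| Ugly-duckling detection | Features from the last layers of that classifier |
| Lesion risk assessment | Uses the classifier's diagnosis |
| Explainable AI | Pixel-level relevance for the diagnostic model's predictions |

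The step itself is a commitment. The link to the classifier is an inference from the order of the sections.

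**Step 2. Is the tuning image like the target image?** The diagnostic annotation section says that body photographs have lower resolution than dermoscopy. Image acquisition shows that the two come from different devices. Resizing, blurring and noise imitate a loss of resolution. They do not imitate the change of device.

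**Step 3. Is the benefit tested?** The experiment named in the classification section compares network variants, not original with super-resolved crops. The data-splitting section reserves a validation set for tuning but does not mention this comparison. The explainable AI section plans to find and correct reliance on data artefacts. Its example is skin markings, and it does not mention generated detail.

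**Step 4. Could the existing data settle it?** Inputs are from Sample size and Data splitting.

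- Melanomas, the plan's own figure first: 75 × 0.003 + 250 × 0.012 + 175 × 0.028 = 0.225 + 3.0 + 4.9 = 8.125, which reproduces the stated 8.
- Keratinocyte cancers, at 67 per melanoma on the rounded group counts: 67 × 0.2 + 67 × 3 + 67 × 5 = 13.4 + 201 + 335 = 549.4, which reproduces the stated 549.
- Validation share of 20%: 0.20 × 8 = 1.6 melanomas and 0.20 × 549 = 109.8 keratinocyte cancers.
- Test share of 15%: 0.15 × 8 = 1.2 and 0.15 × 549 = 82.4.

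This assumes that each cancer counts once and that cases fall in proportion to the split.

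For a paired comparison on the same lesions, take the exact two-sided McNemar test. If all k discordant lesions favour the same input, p = 2 × 0.5^k. With k = 5, p = 0.0625; with k = 6, p = 0.031. At least six discordant lesions are therefore needed for p < 0.05.

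- Melanoma: 1.6 cases cannot supply six discordant lesions.
- Keratinocyte cancers pooled: 6 / 110 = 5.5 percentage points is the smallest difference that could reach p < 0.05, in the best case of one-directional discordance.
- Table 1 separates basal cell from squamous cell carcinoma, and the article does not divide the 549. As an assumed range, a class with half of the 110 (55) would need 6 / 55 = 10.9 points, and one with a quarter (27) would need 6 / 27 = 22 points.
- Nevi: the three stated components sum to 2,400 + 20,000 + 33,075 = 55,475, of which 20% is 11,095. The printed total is higher (66,475), so numbers are ample either way.

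**The case against.** The strongest reply is that comparing one preprocessing step with and without is detail for a fuller development plan, and a condensed article may leave it out. The validation set exists for such tuning, and the article says only that the step can help. This stands for the missing comparison taken alone. It does not cover the commitment itself: the article fixes a generative step whose target is another modality and offers an unverified benefit as the reason.

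Other limits also stand:

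- The tuning data include degraded dermoscopy, so it may not be the only source. The article does not say that the study's own mapped dermoscopy is unused.
- The explainability work is a partial safeguard.

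A reader might also infer more than the documents support:

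- That test accuracy is biased. If training and test crops are processed alike, this step alone does not bias it.
- That labels no longer match inputs, because "The diagnostic classes for annotation were selected to be appropriate for the lower resolution of TBP images (as compared to dermoscopy". That sentence explains the choice of classes. The label is a diagnosis of the lesion, and sharpening the crop does not change it.
- That change detection is contaminated. Its section compares segmentation masks and colours within them, and super-resolution is described only for lesion crops.
- That the Discussion condemns the tuning source when it says that public datasets may "lack generalizability to day-to-day clinical practice". That remark concerns classifiers developed on such datasets.
- That a number of false positives, or a share of invented pixels, can be quoted. Neither the upscaling factor nor any loss of specificity is given, so such figures would be pure assumption.

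**Conclusion.** The point holds as an unverified design choice. The plan commits to a generative step that can add structure the photograph did not record, and it takes the gain for granted. Harm is possible but not shown. The risks are unfaithful detail, poorer transfer to other images, and explanations that point at generated structure.

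The conclusion rests on two readings: that the classifier receives the super-resolved crops, and that degraded dermoscopy is a material part of the tuning data. Its effect on performance cannot be sized from the article. What can be sized is the comparison that would settle the choice of input. It is feasible for benign classes and for keratinocyte cancers with about 110 validation cases pooled, and not feasible for melanoma with 1.6.

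**What to change.** - In the Super-resolution and Skin lesion classification sections, state which crops the classifier receives and whether 210 × 210 pixels is before or after super-resolution.
- Train and evaluate the same classifier on original and super-resolved crops of the same lesions, using the existing training and validation sets. Report paired results per class.
- Adopt super-resolution only if it improves performance in the classes with enough cases, naming those classes before the comparison is run. Otherwise use the original crops. Say plainly that melanoma numbers cannot decide it.
- Where super-resolution is kept, show each explanation map beside the original crop. For lesions that already have mapped dermoscopy, check that the generated structure is present there. The article does not say how many such lesions exist.

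The cost is extra training and validation runs and, if the step is dropped, images that look less like dermoscopy. No new participants are needed.

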#### Skin lesion classification

The outcomes of the previous steps generate datasets containing cropped single-lesion images. To make use of this data and their corresponding diagnostic annotations, we employ a multi-class classifier to automatically identify skin lesions. This classifier categorizes the skin lesions into the classes provided in Table 1. Given that the provided images are approximately 210 × 210 pixels in resolution, we opt for smaller deep learning models designed for handling such dimensions efficiently.

Given the established success of EfficientNet in tasks related to skin cancer detection, our approach involves the utilization of EfficientNet models, specifically choosing from smaller variant models B0, B1, B2, or B3 with fewer parameters for the analysis of our dataset. EfficientNet have demonstrated notable efficacy in achieving accurate results while managing computational efficiency. The flexibility of selecting among these variants allows us to tailor the model to the specific characteristics of our data, ensuring optimal performance in skin lesion diagnosis.

The choice of the final EfficientNet model is still pending, awaiting experimental evaluation to determine the most effective model considering the image resolution. However, the smaller EfficientNet models, in comparison to cutting-edge alternatives, are considered well-suited for application in TBP. Their smaller size not only aligns with the need for speed in this task but also ensures efficiency without compromising performance in the diagnosis of skin lesions.

#### Comparative analyses and ugly duckling detection (nevus phenotype)

Most individuals exhibit a predominant type of nevus (e.g., signature nevus), sharing a similar clinical (or dermoscopic) appearance. Lesions outside of this common pattern in a given individual (i.e., the ugly duckling), must be considered with suspicion, even if it does not fulfill the ABCDE or dermoscopic melanoma-specific criteria. Conversely, an atypical lesion may be completely normal in an individual whose skin is covered with similar lesions in the context of atypical mole syndrome (33, 34). The lesion classification model’s feature extraction capabilities are harnessed to identify “ugly ducklings.” This is achieved by computing the features of individual moles and comparing them with those of other lesions within the same exploration.

Upon mole detection, feature extraction is applied to all potential lesions. This entails computing the output of the last layers of the classification CNN model. To streamline the problem and retain only the most informative features for lesion description, Principal Component Analysis (PCA) (35) is carried out. Subsequently, the L2 norm is employed to calculate a similarity score between each pair of lesions. Any lesion that significantly differs from the rest (indicated by a low similarity score relative to other lesions) is flagged as a potential “ugly duckling.”

#### Lesion change detection

A similar strategy used in inter-exploration lesion matching is applied to match the same lesion across different image captures of the same patient. First, a 3D-based hint for matching skin lesions is computed, and then further refined through a subsequent image-based matching phase involving candidate skin lesions located within the predicted area.

The VECTRA WB360 3D model is transformed into a generic human avatar by fitting a Parametric Body Model (PBM) to the patient’s scan. The PBM serves as an intermediary layer between different explorations (i.e., image captures), allowing lesion positions to be mapped to the avatar and then matched to the next exploration. This position estimation is further refined by performing feature matching on the corresponding images.

Upon identifying lesion matches between the two explorations, changes in color, shape, and size are assessed, as well as pinpointing any newly appearing lesions. To analyze shape and size variations, the segmentation masks computed in the previous algorithms are registered and compared, as depicted in Figure 4. For color changes, the RGB intensities detected within the lesion mask are categorized into color groups including black, white, blue-grey, light brown, dark brown, and red, as illustrated in Figure 5. This categorical segmentation is then compared between both time points, yielding a quantification of color changes.

**Figure 5 fig5:**
[figure not shown]
Color detection of selected skin lesions. Two examples of original skin lesion images **(A,B)**, and subsequent color detection applied **(C,D)**. This step is used to compare sequential explorations of lesions to detect changes in color.

#### Genetic risk assessment

Patient samples (either blood or saliva) are used to extract DNA for genetic risk assessment for melanoma. Previous Genome Wide Association Studies (GWAS) have identified several single nucleotide polymorphisms (SNPs) associated with melanoma risk (36, 37). Most of these SNPs are located in genes associated with skin pigmentation, nevus lifecycle, DNA repair and telomere length. Each individual SNP represents only a small incremental change in melanoma risk, however the cumulative effect, calculated as a polygenic risk score (PRS), is estimated to contribute as high as 30% of melanoma susceptibility (38). Previous methods are used to calculate the PRS based on the reported incremental contribution of SNPs as genetic risk factors (36, 39). Additionally, the applicability of AI-based methods for genetic risk assessment will be explored. Preliminary results show that AI-based methods are quite effective in discovering potential complex interaction patterns among a large number of SNPs.

In addition to SNP analysis for polygenic risk, participants who meet familial melanoma testing criteria (40) are offered genetic testing for genes associated with high risk of hereditary melanoma. Pathogenic variations in these genes are associated with a >50% lifetime risk of melanoma (41). Inheritance of these variations follow an autosomal dominant pattern, meaning first-degree relatives of a carrier will have a 50% chance of harboring the same pathogenic variation. The detection of a pathogenic variation will be included as patient metadata to contribute to risk profiling. The actual variant details will not be released by the clinical sites, only the presence of a high-risk variation will be reported (e.g., yes/no).

